### Diagnostic interview

Panic Disorder is assessed using the Romanian adapted version of Psychiatric Diagnostic Screening Questionnaire (PDSQ) [88, 89], which comprises a self-report screening scale, followed by a semi-structured interview delivered by a clinician. The PDSQ scale has good psychometric properties. In the Romanian validation study the mean of the alpha coefficients was .85 and test–retest reliability was above .80 for nine subscales, with a mean test–retest of .85 [89]. A diagnosis of Panic Disorder is considered if the participant’s score reaches a value of at least 4 on the Panic scale. The same cutoff is applied for agoraphobia. Among Romanian psychiatric patients, these values offered the best balance between sensitivity and specificity: .90/.72 for panic disorder, and .95/.85 for agoraphobia [89].

Following the screening procedures, all eligible participants are interviewed by one of three experienced licensed clinical psychologists, based on the semi-structured interviews included in the PDSQ. This interview has been developed based on DSM-IV diagnosis criteria. In addition to Panic and Agoraphobia diagnoses, any other mental disorder that reached PDSQ screening cutoff point is assessed during the interview. In order to increase inter-raters agreement on assessment protocol, the assessors also participated in a two days training before study commencement. The diagnostic interviews are conducted before and after treatment by clinicians blind to the treatment group. At post-treatment diagnostic interview we are going to count missing data as equivalent to still meeting diagnostic criteria for panic disorder. This is the procedure that is recommended according to the intention-to-treat paradigm and was used in several other studies (e.g. Hedman et al. [42]).

### Secondary outcomes

Secondary outcome measures include quality of life, stress levels, depressive symptoms, catastrophic cognitions, body vigilance, and fear of bodily sensations.

#### Depression

The Patient Health Questionnaire (PHQ-9) is a widely used measure for depression. PHQ-9 contains nine items and covers nine criteria listed in the *Diagnostic and Statistical Manual of Mental Disorders,* 4th Edition (*DSM-IV*), in regard to depression [90], requiring respondents to rate the frequency of present difficulties during the past 2 weeks. Scores indicate presence and severity of depression, with a maximum score of 27 and a minimum score of 0. Scores of 5, 10, 15, and 20 indicate mild, moderate, moderately severe, and severe depression, respectively. The internal reliability of the English version of the PHQ-9 in a clinical population was in the range of 0.86–0.89 [90], which indicates good reliability. The test-retest reliability was also good, 0.84, and the correlation with interview results is very high, 0.84. Furthermore, sensitivity to change — an essential characteristic of measures used to monitor response to treatment — has been repeatedly established [90].

#### Functional impairment

Mundt, Marks, Shear, and Greist [91] developed the Work and Social Adjustment Scale (WSAS). The WSAS is a 5-item simple, reliable and valid measure and we chose it in order to evaluate the self-reported functional impairment produced by anxiety problems. The scale items encompass different domains of functioning and include the following: ability to work, home management, social leisure, private leisure, and ability to form and maintain close relationships. Each item is rated on a 9-point Likert-type scale, ranging from 0 (no impairment) to 8 (very severe impairment). The maximum total score is 40, with higher scores representing greater impairment. The WSAS has demonstrated good internal consistency (range between 0.70 and 0.94) and test-retest reliability (0.73) and is sensitive to patients’ perceptions of disorder severity [91].

#### Attention biases

Body Vigilance Scale (BVS) [92] . We chose this scale in order to detect any changes in attention vigilance toward body sensations, a problem targeted in our treatment program. The 4 items of BVS measure the degree of attentional focus on, and perceived sensitivity towards changes in bodily sensations, and the amount of time spent scanning for bodily sensations. Research suggests that the BVS has adequate internal consistency in clinical and nonclinical populations and can be used to assess changes in bodily attention during cognitive–behavioral treatment for panic disorder [92–94].

#### Fear of body sensations

Body Sensations Questionnaire (BSQ) [95]. BSQ was chosen in order to measure the “fear of anxiety” concept, an aspect that it is targeted in our intervention program. This is a 17 item self-report questionnaire and is used to assess the degree to which sensations associated with autonomic arousal (e.g., “feeling short of breath,” “heart palpitations”) are experienced as frightening. Each item is rated on a five-point scale ranging from 1 (not at all) to 5 (extremely). The BSQ has good internal consistency (*α* = 0.89) and high test–retest reliability (*r* = 0.79) [96]. BSQ is also sensitive to changes following treatment, so it is considered to be a good choice for measuring treatment outcomes [95].

#### Catastrophic cognitions relevant to panic attacks and agoraphobia

Panic Attack Cognition Questionnaire (PACQ). The PACQ [97] is a 25-item scale assessing the extent to which catastrophic cognitions dominated subject’s thoughts before, during, or after panic attacks. Participants are asked to rate each thought on a 4-point scale indicating their level of preoccupation with that thought from 0 = not at all to 3 = totally dominates my thoughts. The total PACQ score is the sum of the 25 item scores. This scale was composed from items generated from the DSM-III-R description of panic attacks, from ideation reported in the anxiety literature, and from interviews with patients. The fifth edition of DSM is currently in use, but analyzing the DSM versions, we could conclude that the panic disorder diagnostic criteria have not changed much from DSM-III-R to DSM-5 (APA, 2013). There is still the distinction between autonomic nervous system symptoms (11 symptoms) and catastrophic cognitions (fear of dying, fear of losing control or going crazy). In the DSM-5 panic disorder and agoraphobia are two separated diagnoses, but other than that there are no major changes, at least not concerning the catastrophic cognitions, which are assessed through PACQ. The PACQ has good internal consistency as calculated by Cronbach alpha (.88). It has also been shown to successfully differentiate between individuals with and without panic attacks [97].

Agoraphobic Cognitions Questionnaire (ACQ) [95]. The ACQ is a 14 item self-report questionnaire, which assesses the frequency of frightening or maladaptive thoughts about the consequences of panic and anxiety. Each item is rated on a five-point scale ranging from 1 (thought never occurs) to 5 (thought always occurs when I am nervous). The ACQ has shown good internal consistency (*α* = 0.82) and test–retest reliability (*r* = 0.79) [96]. ACQ was also proven to be sensitive to changes following treatment [95]. Both measures, PACQ and ACQ, were chosen because they measure catastrophic cognitions relevant to panic disorder and agoraphobia, a very important aspect that is directly targeted in our treatment.

#### Perceived stress

Perceived Stress Scale – 10 (PSS-10) is a short and easy to use questionnaire which proved acceptable psychometric properties and is recommended for the assessment of perceived stress, both in practice and research [98]. PSS-10 [99] measures the degree to which one perceives aspects of one’s life as uncontrollable, unpredictable, and overloading. Participants are asked to respond to each question on a 5-point Likert scale ranging from 0 (never) to 4 (very often), indicating how often they have felt or thought a certain way within the past month. Scores range from 0 to 40, with higher composite scores indicating greater perceived stress. The PSS-10 has demonstrated good internal consistency (0.89) and also good divergent and convergent validity [98, 100].

### Additional measures

#### Treatment credibility and patient expectancies

The Credibility/Expectancy Questionnaire (CEQ) of Devilly and Borkovec is used to measure expectancy for change and treatment credibility. It comprises six questions, four on “thinking” and two on “feeling” and they are rated on a Likert-type scale from 1 to 9. The scale has shown good internal consistency (expectancy, α = .79–.90; credibility, α = .81–.86) and test–retest reliability (expectancy, 0.82; credibility, 0 .75) [101]. CEQ is administered twice; after the first and the fourth Skype session for the guided participants, and at 2 and 6 weeks during intervention for the unguided participants.

#### Working alliance

Working Alliance Inventory-Short Form (WAI-S) [102, 103]. The WAI-S is a 12-item client self-report measure to assess the working relationship and therapeutic bond between client and therapist. This measure is commonly used in CBT treatment outcome studies’, including those in which treatment is delivered remotely. The 3 subscales are: agreement on goals for treatment, agreement on therapeutic tasks, and perception of therapeutic bond. Ratings are given on a 7 - point Likert scale, with higher scores reflecting a stronger working alliance. Busseri and Tyler [104] reported that the WAI - S has good internal reliability for the composite score (alpha = .91) and the subscales (alpha = .73 to .86). WAI-S is administered twice, after the first and the fourth Skype session, according to existing recommendations [105].

#### Personality traits (dependent personality and personal autonomy)

OMNI-IV [106]. Derived from the 375-item OMNI Personality Inventory, the 210-item OMNI-IV measures abnormal personality traits and assesses personality disorders. It is composed of 10 Personality Disorder scales based on the DSM-IV Axis II personality disorder criteria. For our study we use the Dependent Personality Subscale, which has 15 items. Previous studies showed good internal consistency, α = .80–.82 and also test-retest reliability, 0.80–0.84 [106]. In the Romanian sample used to validate the scale internal consistency varied between 0.79 and 0.88 and test-retest reliability was 0.67 [107].

Personal Autonomy Questionnaire (PAQ) [108]. The PAQ is a 36-item questionnaire designed to measure four dimensions of personal autonomy: cognitive autonomy, behavioral autonomy, emotional autonomy and value autonomy. Ratings are given on a 5-point Likert scale, with higher scores reflecting a stronger personal autonomy (reverse score items: 1, 4, 12, 13, 14, 15, 19, 29, 34, 35 and 36). PAQ has good internal consistency, α = .80 and also test-retest reliability, 0.86. [108].

#### Perceived social support

The SS-5 is an abbreviated version of the Medical Outcomes Study Social Support Scale (MOS-SSS) [109]. This is a 5 item short and reliable measure for assessing perceived social support, a putative predictor or moderator of treatment outcome. Each item is scored on a 5-point Likert scale and the items are summed for a total score ranging from 5–25. The SS-5 proved to have adequate test-retest reliability (0.92) and internal consistency (α = .88). Equivalence between paper and web-based administration has also been demonstrated [110].

#### Usability

The System Usability Scale (SUS) is one of the oldest questionnaires used to evaluate usability of a system and was designed in 1986 by Broke. The SUS consists of 10 items scored on a 5-point Likert scale (1-5), with odd-numbered items worded positively and even-numbered items worded negatively. The scale has been used in hundreds of studies and the psychometric qualities are adequate (α = .88). For many years the scale was considered unidimensional, but recent studies have shown that it measures not just usability, but also learnability of a new system [111].

#### Sociodemographic questionnaire

To evaluate the sociodemographic characteristics of the participants, we used a 7 questions survey referring to: environment (urban or rural), ethnicity, marital status, education, occupation, income levels and computer skills (1 to 10).

#### Psychoeducation

Psycho-Education Questionnaire (PEQ)*.* In order to evaluate the information participants have about panic disorder and its treatment, we used a brief knowledge test that consisted of an 8-item questionnaire. Seven of the questions used are multiple choice questions and the last one is a self-evaluation question concerning the level of knowledge about PD and its treatment (from 1 – “I don’t know anything”, to 10,” I know almost everything”).

#### Adherence to treatment and homework compliance

Adherence to treatment and completion rates will be assessed. Number of modules completed, time spent in total, time spent on each module, and usage of the support will be analyzed to identify potential mediating effects.

#### Frequency of use of anxiety reduction strategies

In order to assess how frequent the anxiety reduction techniques were used we have developed a 10 items questionnaire. Eight of these questions are scored on a 5-point Likert scale (0-never and 4-daily or almost daily) and the last two are open ended questions: “Which techniques helped you the most?” and “Which are the techniques that you plan on using after the end of the intervention?”

#### Patient satisfaction

The Patient Feedback Questionnaire (PFQ). We have developed a 14-items questionnaire to evaluate the patients’ satisfaction with the platform and some other aspects (the quality and utility of different components of the platform). Other items refer to giving improvement suggestions, what they like most, if they would use it again or recommend it to a friend with anxiety problems.

#### Drop-out reasons

In order to find the reasons or motives participants had for dropping out of the study, we have developed an 18-item questionnaire. Each item is considered to be a possible motive (e.g. lack of motivation, lack of time, different expectations, exacerbation of symptoms, interface is too complicated, the treatment pace is too slow or too fast, finding another treatment, getting better, important life events etc.).

### Randomization

Participants who return the informed consent and meet all the required criteria are randomly allocated to one of the three conditions (1:1:1 allocation ratio). The randomization process is done by a software that was developed to implement a minimization algorithm [112], that assures a balanced randomization between groups with respect to certain predefined prognostic (stratification) factors. In this study, two stratification factors have been considered: SEVERITY (3 levels according to PDSS-SR screening scores; level 1: 6 to 13 points; level 2: 14 to 20 points; level 3: 21 to 28 point) and CHRONICITY (2 levels; more or less than 6 months since the beginning of PD) of panic disorder. The minimization method has been shown to outperform simple randomization in achieving balanced groups [113] and its use in clinical trials has been previously recommended as a better option than other randomization methods (e.g. [113–115]). Before each allocation, the algorithm computes an imbalance score for the three available treatments, taking stratification factors levels into account. The treatment with the lowest imbalance score is then given preference when assigning treatments, but the allocation probability varies for each patient, depending on the actual level of imbalance [116]. This method is preferred because it avoids the deterministic allocation of pure minimization [117]. The allocation is done by an independent researcher and is concealed, i.e. patients and researchers have no knowledge and no control over the allocation of participants when they randomize a participant with the computer program.

### Blinding

Taking the characteristics of our research into consideration, it is impossible to keep patients or psychotherapists blind to the study procedures and intervention. All participants are provided with detailed information about the aims and the methodology of the study. They can request more information about the study and they have the right to terminate participation at any time. The personnel in charge with the clinical interviews, on the other hand, will be blind to the treatment group allocation. We specifically instruct the participants not to mention group allocation at the post-treatment interview, but also test whether blinding was successful. The clinicians who conduct the diagnostic interviews are required to describe in their report if the participants disclosed their study group, directly or indirectly.

### Sample size

The effect sizes reported between guided and unguided interventions are quite heterogeneous with small to medium Cohen’s d size effects between 0.27 [64] and .42 [14]. Taking into consideration that, in most part, the guidance in previous studies was in fact low-intensity guidance, and that more support from a therapist yields larger effects [21, 62, 63], we expect an effect size of 0.5 (Cohen’s d) between guided and unguided treatment for PD. Based on this effect size, a power of 0.80, and an alpha level of 0.05, we would need 51 subjects in each condition. This recommended sample size has been increased to accommodate an attrition rate of 20 %. Thus, the study aims to achieve a sample of 192 participants.

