### Primary outcomes

The primary outcomes are the diagnostic status of the participants at post-assessment and symptoms of panic disorder as assessed with the PDSS-SR.

Panic Disorder Severity Scale – Self Report (PDSS-SR). PDSS is originally a face-to-face interview and was adapted to a self-report questionnaire by Houck et al. [87]. The scale contains seven items that measure the severity of seven dimensions of panic disorder and associated symptoms: 1) frequency of panic attacks; 2) distress during panic attacks; 3) anticipatory anxiety (worry about future panic attacks); 4) agoraphobic fear and avoidance; 5) interoceptive fear and avoidance (i.e., apprehension and avoidance of bodily sensations); 6) impairment of or interference with work functioning; and 7) impairment of or interference with social functioning. The PDSS-SR generates a total score ranging from 0 to 28, with a higher score indicating more severe panic symptoms. The questionnaire has good psychometric properties (Cronbach’s alpha = 0.92, test-retest reliability is 0.83) and is sensitive to changes following treatment [87]. A cut-off score of six may discriminate between the presence and absence of current DSM-IV panic disorder and a cut-off score of fourteen may discriminate between mild and severe panic disorder [82].

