### Statistical analysis

All statistical analyses will be performed using the IBM SPSS Statistics version 20. The main analyses will be conducted on the intention-to-treat samples (all randomised participants, regardless of protocol adherence). Following current standards [27, 28], a linear mixed effects models approach with full information maximum likelihood estimation will be used. This approach has been recommended since it uses all available data and can handle missing data appropriately [118, 119]. The approach is based on the assumption that data are missing at random, and does not assume that missing data remain stable, as in the last-observation-carried-forward (LOCF) approach [119, 120]. Significance testing of dichotomous data such as diagnostic status will be conducted with chi-square tests. Calculations of within- and between-groups effect sizes (Cohen’s d) will be based on the pooled standard deviations. Regression analyses will be used to identify predictors of treatment outcome. Moderation and mediation analyses will be conducted with multiple regression models, using the PROCESS macro for SPSS [121], a computational technique that can compute both simple and complex moderation and mediation models. Effect sizes for significant effects will be indicated by Cohen’s f.

Consistent with CONSORT [77] and SPIRIT [78] recommendations we mention our intention to perform secondary analyses for minimal treatment users, defined as participants that complete at least 5 of the recommended modules, have at least 3 of the available guidance sessions (this is available only for the Skype-guided group) and use the intervention program for at least 80 min. This definition is based on the specific of our intervention program and the criteria used in other studies [27, 119].

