Several possible limitations should be noted. Firstly, the study sample size is large enough to reach our main research objectives, but will not permit us to perform detailed subgroup analyses. However, we expect to identify candidate predictors of treatment outcome that could be tested directly in future studies with larger samples. Secondly, the control group, for ethical reasons, will receive treatment in the second stage of the trial, thus the control group will not be available at follow-up. Furthermore, most of the recruitment will be made from the community, through advertisements in the media and on the study website, which could lead to a self-selected sample. Regarding the latter limitation, several findings from recent studies suggest that sampling bias may not affect the generalizability of internet-based trials. For example, Titov et al. [122] revealed that patients undergoing web-based treatments resemble national samples and present disorders as severe as those undergoing traditional psychotherapy. Another example is a recent study by Donkin et al. [123] on sampling bias in an internet-based clinical trial for depression. The authors revealed that out of 35 potentially biasing factors, only 4 were associated with consenting likelihood, accounting for limited variance in explaining participation, and none were associated with the primary outcomes. Future research will be required, nonetheless, to investigate whether the results from the PAXonline trial can be generalized to samples in regular mental health care settings.

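### The single power statement is a two-means calculation; its 80% does not carry over to diagnostic status, the other primary outcome, which is tested by chi-square with dropouts kept as failures

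*Protocol article*

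**What the plan says.** Primary outcomes section: "The primary outcomes are the diagnostic status of the participants at post-assessment and symptoms of panic disorder as assessed with the PDSS-SR". The Abstract also lists both as primary.

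Sample size section, the only power statement: "we expect an effect size of 0.5 (Cohen’s d) between guided and unguided treatment for PD", then "Based on this effect size, a power of 0.80, and an alpha level of 0.05, we would need 51 subjects in each condition". It continues: "This recommended sample size has been increased to accommodate an attrition rate of 20" per cent, and "Thus, the study aims to achieve a sample of 192 participants". It names no outcome, no recovery rate and no sidedness.

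Statistical analysis section: the main analyses include everyone randomised, and "Significance testing of dichotomous data such as diagnostic status will be conducted with chi-square tests".

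Diagnostic interview section, on the post-treatment interview: "we are going to count missing data as equivalent to still meeting diagnostic criteria for panic disorder".

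Discussion, on limitations: "the study sample size is large enough to reach our main research objectives". This is not restricted to either primary outcome.

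**The concern.** Two things the article fixes do not fit together.

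1. **Test.** A formula for two means on Cohen's d does not size a chi-square test. Reducing a continuous difference to recovered or not recovered loses information, so the same underlying effect is detected less often.
2. **Attrition.** Going from 51 to 64 per arm assumes that the 20% who drop out leave the analysis, so that 51 remain. For diagnostic status they stay in the denominator as failures. With equal dropout this pulls the two recovery proportions together, and the extra 13 per arm do not make up for it.

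Diagnostic status is the only primary outcome rated by blinded assessors; the PDSS-SR is self-reported by participants who know their group. A reader who applies the 80% to both outcomes could give a non-significant guided–unguided chi-square more weight than the design supports.

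**Working it through.** **Inputs from the article.** d = 0.5; power 0.80; alpha 0.05; 51 per arm; 20% attrition; 192 in total at 1:1:1, so 64 per arm; chi-square test; missing counted as still diagnosed.

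**Inputs assumed, because the article gives none.** True unguided recovery of 20–70%. Conversion of d = 0.5 to a difference in recovery in two ways: an odds ratio of exp(0.5 × π/√3) = 2.48, or a shift of 0.5 SD on the probit scale.

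**Step 1: reproduce the plan's figure.** n per arm = 2(z₁₋α + z₀.₈)²/d².
- One-sided: 2(1.645 + 0.842)²/0.25 = 49.5; the t-based value is 50.2, so 51. Then 51/0.8 = 63.75, so 64, and 3 × 64 = 192. This matches.
- Two-sided: 62.8; the t-based value is 63.8, so 64 before attrition. This does not match. At 51 per arm the two-sided t-test has about 71% power.

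The plan's arithmetic therefore holds as a one-sided comparison of means. Sidedness is a separate question, so both versions are shown below.

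**Step 2: effect of the missing-data rule.** With dropout q in each arm, the analysed recovery rate is (1 − q)p, so the difference becomes (1 − q)(p_G − p_U). At q = 0.20 it shrinks by a fifth. Example: unguided 40% has odds 0.667; multiplied by 2.48 this gives 1.65, or 62% guided. Multiplying both rates by 0.8 gives 32% versus 50%, and the difference falls from 22 to 18 points.

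**Step 3: power for diagnostic status.** Exact binomial enumeration of the chi-square test without continuity correction, 64 per arm, 20% missing as failure in each arm. Each cell gives odds-ratio / probit conversion.

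| True unguided recovery | Implied guided recovery | Two-sided power | One-sided power |
|---|---|---|---|
| 20% | 38% / 37% | 50% / 44% | 63% / 57% |
| 30% | 51% / 49% | 56% / 46% | 68% / 59% |
| 40% | 62% / 60% | 55% / 46% | 65% / 57% |
| 50% | 71% / 69% | 47% / 40% | 60% / 52% |
| 60% | 79% / 77% | 40% / 35% | 51% / 46% |
| 70% | 85% / 85% | 31% / 29% | 41% / 39% |

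**Step 4: separate the causes, one-sided throughout.** The t-test on 51 per arm has 81% power. The chi-square on 51 complete cases per arm has 56–72%. The chi-square on 64 per arm with 20% counted as failures has 39–68%. The change of test and the missing-data rule both cost power, without any change of sidedness. Two-sided, 51 complete cases give 43–65%, and 64 with no dropout at all give 52–71%.

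**Step 5: unequal dropout averaging 20%.** The analysed difference is now (1 − q_G)p_G − (1 − q_U)p_U, which widens if the unguided arm loses more.

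| Dropout, unguided vs guided | Two-sided power | One-sided power |
|---|---|---|
| 20% vs 20% | 29–56% | 39–68% |
| 22% vs 18% | 42–64% | 54–75% |
| 25% vs 15% | 59–76% | 71–84% |
| 30% vs 10% | 73–92% | 83–95% |

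The ranges cover unguided recovery of 20–70% and both conversions.

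**The case against.** **The article never claims 80% for diagnostic status.** This stands. The figure is attached to Cohen's d, which belongs to a continuous scale, and the measurement table lists the PDSS-SR alone as the primary outcome measure among the self-report ratings. A reader might infer that the article states 80% for both primary outcomes and is wrong; the text does not support that. What remains is that it names no outcome, has two primary ones, and then calls the sample adequate without qualification.

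**Setting 80% against 29–56% mixes two issues.** This also stands. The 51 reproduces only one-sided, so the like-for-like comparison is 39–68%. The rest of the gap is sidedness.

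**Equal dropout may be the wrong assumption.** A reader might infer from the equal-dropout figures that no plausible scenario reaches 80%. That does not hold. The Background reports literature favouring guided treatment on dropout, and higher unguided dropout raises power, past 80% in some cases. Against this, the Sample size section plans a single 20% rate, and the gain would come from imputed failures rather than observed non-recovery.

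**Guided versus unguided is labelled a secondary objective.** It is, in the Objectives section. But the trial was sized on this comparison, and the Discussion calls the added effect of guidance a central focus. Nothing here shows that the sample is too small for comparisons with the waiting list, which were not assessed.

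**This could be left to the analysis plan.** The outcomes, the test, the missing-data rule and the power statement all stand in the article; the point concerns how they fit together.

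**Conclusion.** The concern holds in limited form. The stated 80% describes a comparison of means and fits the PDSS-SR; it does not carry over to diagnostic status. With the planned 20% dropout in each arm, guided–unguided power for that outcome is about 39–68% one-sided or 29–56% two-sided at 64 per arm. These ranges rest on assumed unguided recovery of 20–70%, two assumed conversions of d = 0.5, and equal dropout. The last matters most: at 25% versus 15% the two-sided range is 59–76%, and at 30% versus 10% it is 73–92%. The plan's own arithmetic is not in error on a one-sided reading. This is a matter of the scope of the power statement and does not show that the trial is too small for all its aims. It should be corrected because the correction is cheap and concerns the one blinded primary outcome.

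**What to change.** - **Sample size section:** state that the calculation and its 80% refer to the PDSS-SR comparison of guided with unguided treatment.
- **Same section:** add the power of the chi-square test of diagnostic status at 64 per arm under the missing-as-failure rule, giving the assumed recovery rates, the sidedness, and a range over equal and unequal dropout.
- **Discussion:** for the guided–unguided comparison, limit the sentence on adequate sample size to the PDSS-SR.
- **Optional:** report the guided–unguided result for diagnostic status as a risk difference with a 95% confidence interval.

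The cost is a few sentences and a short calculation. No extra patients and no design change are needed. The downside is a less favourable stated power for one primary outcome.

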### Study design

This study is a randomized controlled trial with two active treatment conditions and a waiting list control group. A one-factor experimental design (parallel-group, superiority trial) will be used. The three conditions are:*Web-based self-help program for panic disorder with intensive guidance (PAX-guided)*: participants in this group will complete the PAXonline panic disorder treatment program with support from a therapist, which include weekly emails and regular 15-30 min Skype sessions. In total, there will be 10 Skype sessions available.*Web-based self-help program (PAX-unguided)*: participants in this group will complete the PAXonline panic disorder program in a self-guided format, i.e. without any support from a therapist.*Waiting list control group*. This group will not receive any treatment for 12 weeks. At the end of the waiting period, the participants receive any of the two treatment programs, depending on their choice.

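### The 51 per arm behind N = 192 matches only a one-sided t-test, which the article does not declare; an unadjusted two-sided comparison of 51 per arm has about 71% power

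*Protocol article*

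**What the plan says.** The Sample size section sizes the trial on one contrast only: "we expect an effect size of 0.5 (Cohen’s d) between guided and unguided treatment for PD". It continues: "Based on this effect size, a power of 0.80, and an alpha level of 0.05, we would need 51 subjects in each condition". The figure is then raised for 20% attrition, giving 192 participants over three arms allocated 1:1:1 (64 per arm). The section says nothing about the direction of the test.

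The other relevant sections do not settle it. Study design states: "A one-factor experimental design (parallel-group, superiority trial) will be used". Statistical analysis says that for the main analyses, on all randomised participants, "a linear mixed effects models approach with full information maximum likelihood estimation will be used", and that "Significance testing of dichotomous data such as diagnostic status will be conducted with chi-square tests". Neither section declares a one-sided or directional test.

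Among the limitations, the Discussion reassures the reader that "the study sample size is large enough to reach our main research objectives".

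**The concern.** An alpha of 0.05 given without qualification is conventionally read as two-sided, and mixed-model and chi-square tests are ordinarily reported without direction. On that reading d = 0.5 with 80% power calls for 64 per arm, not 51. The stated figure is lower by 13 per arm, about the amount that the attrition allowance adds back.

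At stake is the reading of the guided-versus-unguided result. This is the only comparison used to size the trial, and the Discussion treats it as a central question. If the test is two-sided and unadjusted, the chance of missing a true d = 0.5 is about 29%, not 20%. A non-significant difference would then be weighed against more sensitivity than the calculation supports.

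**Working it through.** **Inputs, all from the Sample size section unless noted**
- d = 0.5 (guided versus unguided), power 0.80, alpha 0.05 with no side stated
- attrition 20%
- three arms, 1:1:1 (Randomization section)

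**Method.** Two-sample t-test with n per arm, df = 2n − 2 and noncentrality d × √(n/2). Power is the probability that the noncentral t exceeds the critical value.

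**Step 1: reproduce the plan's figure**
- One-sided alpha 0.05: n = 50.15, rounded up to **51**. Power at 51 is 0.806.
- Attrition: 51 / (1 − 0.20) = 63.75, rounded up to 64 per arm; 64 × 3 = **192**.

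The whole chain reproduces exactly, and the attrition step is done correctly.

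**Step 2: the same inputs, two-sided**
- n = 63.77, rounded up to **64** per arm (63 by the normal approximation).
- The requirement is 64 / 51 = 1.25 times the stated one.

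**Step 3: another possible origin of 51.** An omnibus three-group ANOVA with f = 0.25 gives 52.4, so 53 per arm. That is close but not equal, and it is not the two-arm Cohen's d comparison that the section describes.

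**Step 4: two-sided power at the planned sizes, unadjusted, d = 0.5**

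| Analysable per arm | Situation | Two-sided power |
|---|---|---|
| 51 | after 20% attrition | 0.706 (normal approximation 0.714) |
| 64 | no attrition | 0.801 |

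For n = 51, noncentrality = 0.5 × √25.5 = 2.52, against a critical value of 1.98 on 100 df. The smallest effect with 80% two-sided power at 51 per arm is d = 0.56.

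**Step 5: what baseline adjustment would recover.** The article gives no baseline-outcome correlation r, so r is an assumption. Adjustment divides the residual SD by its unadjusted value to give √(1 − r²), so the effective effect is 0.5 / √(1 − r²).

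| Assumed r | Effective d | Two-sided power at 51 per arm |
|---|---|---|
| 0.30 | 0.524 | 0.746 |
| 0.40 | 0.546 | 0.779 |
| 0.45 | 0.560 | 0.800 |
| 0.50 | 0.577 | 0.823 |

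The break-even follows directly: √(1 − 51/64) = 0.45.

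**The case against.** **The planned analysis is not an unadjusted t-test on completers.** It is a full-information mixed model on everyone randomised. The PDSS-SR is taken at baseline, mid-treatment and post-treatment, and every two weeks in the two treated arms. Participants who drop out still contribute, so the effective number per arm can lie between 51 and 64, and correlation with baseline can add more. This stands. A reader might infer that the trial's planned tests have 71% power; the article does not support that, because the model's power depends on correlations and a contrast it does not give. For the same reason the model does not rescue the stated 80%: the Sample size section credits no correlation and no repeated measures.

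**Two-sidedness is inferred.** Also true. It rests on convention and on the absence of any one-sided declaration. The chi-square sentence concerns diagnostic status, not the continuous outcome that was sized. The side may be stated in a fuller document. Even so, the section as written is incomplete on the one item that decides whether the figure is 51 or 64.

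**A one-sided test might be defended.** A reader might infer that it is unjustified because the article calls findings on guidance divergent. But the Background also reports a strong tendency in favour of guided treatment, and both published effects cited in the Sample size section are presented in support of guidance. The document does not settle this either way.

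**Low power at the smaller cited effects is a separate matter.** Two-sided power at 51 per arm is 0.556 for d = 0.42 and 0.272 for d = 0.27. One-sided it is still only 0.678 and 0.386. Most of that shortfall comes from planning on d = 0.5, for which the section gives a reason, and should not be charged to the choice of side.

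**Conclusion.** The point holds in a limited form. The stated inputs give 51 per arm only under a one-sided t-test that the article never declares. Under the conventional two-sided reading, the requirement is 64 analysable per arm. An unadjusted two-sided comparison of 51 per arm has about 71% power at d = 0.5, and the allocated 64 per arm reaches 80% only without attrition.

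This rests on a two-group endpoint comparison, on exactly 20% loss, and on reading an unqualified alpha as two-sided. The arithmetic itself is not in doubt.

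A reader might go further and call the Discussion's statement about adequate sample size false. That is not shown. The article's stated aim is the efficacy of the guided programme, with guided versus unguided as a secondary objective, and nothing here bears on power against the waiting list. The statement needs qualifying for guided versus unguided only.

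**What to change.** 1. **Sample size section.** State the side of the test. Say that 51 analysable per arm gives 80% power at d = 0.5 one-sided and about 71% two-sided for an unadjusted comparison, with a smallest effect of d = 0.56 at 80% two-sided power.
2. **Discussion, limitations.** Qualify the claim of a large enough sample for guided versus unguided.
3. **Statistical analysis section.** Pre-specify the week-12 guided-versus-unguided PDSS-SR contrast adjusted for baseline PDSS-SR, which is already collected, and state the correlation assumed. At an assumed 0.30 to 0.50, two-sided power with 51 per arm is 0.75 to 0.82, reaching 0.80 at about 0.45.

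The cost is a less favourable stated power and a small addition to the analysis plan. No extra enrolment is asked for. For comparison, buying 80% two-sided power by numbers alone would take 64 / 0.8 = 80 per arm, or 240 in total. The Trial status section reports 99 recruited by December 2015, so on that date the change could still be made before the data were analysed.
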